**Figure 1: Fig1:**
[figure not shown]
Flow chart of enrolment, allocation and baseline

#### Outcome measurements and statistical analyses

The primary outcome of the RCT is RTW. We will analyze the difference between cases and controls in proportion of patients on full- or part-time sick leave at three, six and 12 months after inclusion. We will use data from the Swedish Social Insurance Agency’s Micro Database for Analyzing Social insurance (MiDAS) where all sick-leaves exceeding two weeks are registered. The intention to treat principle will be followed.

The intervention is designed to facilitate for the caregiver to involve the employer in rehabilitation and strengthen the patient’s RTW-SE, but whether these mechanisms are triggered or not will depend on circumstances among patients, employers as well as the caregivers, i.e it will depend on contextual factors [46]. For example, the effect of the intervention on RTW might depend on the patient’s symptom severity, the employer’s readiness for work adaptation, or on the caregivers’ adherence to the protocol. In order to conduct sub-group analysis within the intervention group, a follow-up questionnaire is sent to the patients’ home address by mail at six and 12 months after inclusion. In addition to questions about the rehabilitation process, the questionnaire contains the same items as the baseline measurement. For example we will explore how gender, age, occupation, symptom severity, employer activities and RTW motivation affect RTW.

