**Methods:**

Twenty-two primary care centers were randomized to either intervention or control group. At the intervention centers, physicians and rehabilitation coordinators underwent training, providing them with both knowledge and practical tools to involve the employer in rehabilitation. At the patient level, employed patients with an ICD-10 F43 diagnosis were eligible for participation (*n*=132). Difference in proportion of patients on full- or part-time sick leave at three, six and 12 months after inclusion will be investigated. Register data, logbooks and interviews with coordinators and physicians at both intervention and control centers will be used for process evaluation.

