### The RCT

#### Target group, recruitment and randomization

The target group for the intervention was GPs and RCs at the included PHCCs, and by extension their patients, sick-listed from work due to a stress-related diagnosis. The recruitment of PHCCs took place between January and October 2016. A first request to the PHCCs to participate were communicated by telephone calls, e-mails and personal meetings with PHCC managers throughout the Västra Götaland region. In order to attain diversity in terms of geographical location, public or private ownership, center size, and the socioeconomic conditions of the area, interested centers were checked against regional register data. We also considered the number of patients with a F43 diagnosis at the center during one year (2015), the center’s involvement in other research projects, and the extent of RC resources at the center.

Out of the 30 public and private PHCCs that were invited to participate, 22 accepted; 15 public and seven private centers. Managers accepted the center’s commitment by signing a contract with the researchers. Managers were asked to make sure that the entire staff agreed to the center’s participation in the study before signing the contract. The researchers visited each center to inform the staff about the study prior to commitment. PHCCs were offered economic compensation for recruited patients; € 50 per patient in the control group and € 100 per patient in the intervention group. Also, all centers were offered the one day training program, however they were informed that if allocated to the control group, they would have to wait until all patients were recruited to the study.

Based on similar characteristics in register data, we matched centers in pairs. From each pair, one center was randomly selected to the intervention group and the other one to the control group. The staff of the participant centers were all aware about their allocation in the RCT, blinding was not possible in this study.

Employed patients with a F43 diagnosis as the main diagnosis, getting their sickness certification renewed were eligible for participation. Excluded were patients with post-traumatic stress disorder, F43.1. Patients who did not read or speak Swedish, and patients who have had a sick-leave period of more than 60 subsequent days during the past three years before inclusion were not asked to participate.

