#### Sample size

In all 135 patients were recruited; 69 to the control group and 63 to the intervention group (see Fig. 1). Depending on the proportion of patients on sick-leave at three, six and twelve months after inclusion, power will vary between 41 % and 74 % (based on the assumption that the prevalence of sick-leave in the control group fluctuates between 20 % and 95 % and with an estimated difference between the groups of 15 % [45]; a two-sided test and a statistical significance of p < 0.05). There was a substantial variation in the number of recruited patients per PHCC.

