## Discussion

Given that patients with stress related disorders constitute the largest and fastest increasing group in the sick-leave statistics in Sweden, there is an urgent need to come up with methods to stop this development. Most of these patients get their sickness certificate issued by a GP in the primary health care system. Although current evidence of how to enhance RTW for CMD patients, including stress-related disorders, is yet inconclusive, many recent reviews point to that employer involvement early on in the process might be an efficient way to reduce sick-leave. However, time constraints and uncertainties about the relationships between work and stress hinder many GPs to involve the employer. RCs have been introduced into Swedish primary health care to support the patient in the RTW process through coordination between different stakeholders. This opens a window of opportunity to develop new procedures and tools. This RCT was designed to contribute to knowledge about how procedures of cooperation between GPs and RCs can be organized to facilitate employer involvement and reduce time to RTW among patients suffering from work related stress. Despite considerable efforts to encourage and support GPs and RCs at the participating centers, it turned out to be difficult to recruit patients. Unless the impact of the intervention on RTW is substantial, it will be difficult to detect a difference in RTW between the intervention and control group with the current sample size (*n*= 132).

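### Matched pairs of centres were randomised, but the stated power treats 132 patients as independent and the primary comparison mentions neither centre nor pair

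*Protocol article*

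**What the plan says.** The unit of randomisation is clear. The abstract of the protocol article states: "Twenty-two primary care centers were randomized to either intervention or control group". The section on target group, recruitment and randomization adds: "Based on similar characteristics in register data, we matched centers in pairs". It continues: "From each pair, one center was randomly selected to the intervention group and the other one to the control group". That gives 22 units in 11 pairs.

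The section on outcome measurements and statistical analyses describes the primary comparison in terms of patients: "We will analyze the difference between cases and controls in proportion of patients on full- or part-time sick leave", at three, six and 12 months, by intention to treat and from national sick-leave register data. It names no test, model or standard-error method. Centre, pair and ICC do not appear there.

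The sample size section gives the patient numbers, "69 to the control group and 63 to the intervention group", and says that "power will vary between 41 % and 74" per cent. This assumes control rates of 20% to 95%, a 15-point difference and "a two-sided test and a statistical significance of p < 0.05". It mentions no design effect, although it notes that recruitment varied considerably between centres. The Discussion likewise judges what can be detected "with the current sample size" of 132 patients, without mentioning the number of centres.

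**The concern.** When centres are randomised, patients of the same centre tend to have similar outcomes, and a test that counts patients as independent understates the standard error of the arm difference. The article itself gives reasons to expect such similarity:

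- The intervention is delivered by each centre's own physicians and coordinator.
- Usual care differed between control centres, since coordinators contacted employers at only some of them.
- The Discussion expects implementation to depend on conditions at the centre.

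Two things are at stake. The first is whether the 5% level and the confidence interval hold, if the final test follows the same logic as the power calculation. The second is whether the stated power describes the trial that was run.

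**Working it through.** **Inputs from the article.** 69 control and 63 intervention patients, total 132. (The sample size section also gives 135 recruited; 69 + 63 = 132 agrees with the abstract and the Discussion and is used here.) 22 centres, 11 pairs. Control rate 20% to 95%, difference 15 points (taken as a reduction, since 95% + 15% is impossible), two-sided alpha 0.05.

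**Assumptions.** The article gives neither ICC nor spread of cluster size. ICC is taken as 0.01 to 0.10 and CV as 0 or 0.8. Mean cluster size is 132/22 = 6.0, which supposes that every centre contributed patients.

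**Step 1: reproduce the stated power.** Pooled z test on independent patients:

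power = Φ[(0.15 − 1.96·SE0)/SE1], with SE0 = √{p̄(1−p̄)(1/69 + 1/63)} and SE1 = √{pC(1−pC)/69 + pT(1−pT)/63}.

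- Control rate 20%, intervention 5%: p̄ = (13.8 + 3.15)/132 = 0.128, SE0 = 0.0583, SE1 = 0.0554. Power = Φ(0.0357/0.0554) = 74.0%.
- Control rate 50%, intervention 35%: p̄ = 0.428, SE0 = 0.0862, SE1 = 0.0851. Power = Φ(−0.0190/0.0851) = 41.2%.
- Minimum 40.5%, at a control rate of about 57%. At 95% the power is 75.0%.

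The stated 41% to 74% is therefore a calculation for individually randomised patients. A continuity correction (34% to 66%), a one-sided test (53% to 84%) and Fisher's exact test (35% to 74%) do not fit at both ends. Any design effect above 1 lowers both ends.

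**Step 2: add clustering, ignoring pairs.** DE = 1 + {(1 + CV²)·6 − 1}·ICC, that is 1 + 5·ICC for equal clusters and 1 + 8.84·ICC for CV 0.8. A test that ignores centre has type I error 2{1 − Φ(1.96/√DE)}. For power, both arm sizes are divided by DE.

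| CV | ICC | DE | Type I error | Lowest power | Power at 20% control rate |
|---|---|---|---|---|---|
| 0 | 0.01 | 1.05 | 5.6% | 39% | 72% |
| 0 | 0.02 | 1.10 | 6.2% | 37% | 70% |
| 0 | 0.05 | 1.25 | 8.0% | 34% | 64% |
| 0 | 0.10 | 1.50 | 11.0% | 29% | 56% |
| 0.8 | 0.01 | 1.09 | 6.0% | 38% | 70% |
| 0.8 | 0.02 | 1.18 | 7.1% | 35% | 67% |
| 0.8 | 0.05 | 1.44 | 10.3% | 30% | 58% |
| 0.8 | 0.10 | 1.88 | 15.3% | 24% | 46% |

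These figures allow neither for a gain from matching nor for the limited degrees of freedom.

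**Step 3: add the matching.** Simulation under the null: 11 pairs, logit-normal centre effects, rate 50%, nominal CV 0.8, 20,000 runs per setting. The ICC here is on the logit scale, so the rows do not correspond exactly to Step 2. Type I error of the patient-level z test, by share of between-centre variance explained by the pairs:

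| ICC | 0% | 50% | 90% |
|---|---|---|---|
| 0.05 | 8.9% | 7.5% | 6.1% |
| 0.10 | 12.4% | 9.9% | 7.3% |

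At ICC 0.01 to 0.02 the figures lie between 5.1% and 6.1%. A paired t test on centre proportions stayed between 4.6% and 5.5% throughout.

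**The case against.** A reader might infer that the plan has chosen to ignore clustering, and that standard errors will therefore be too small. The article does not say so. The quoted sentence defines a contrast, and a difference in proportions can be estimated with a mixed model, GEE or a centre-level test. An article may leave that choice to an analysis plan that is not shown. This stands, and the point on the analysis is conditional for that reason. It does not cover the sample size section, which publishes a calculation for the same contrast and time points that is at odds with the randomisation.

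A reader might also take the upper type I error figures as the expected size. They need an ICC of 0.10, uneven clusters and no benefit from matching. With about 6 patients per centre and a low ICC the inflation is slight, and ignoring effective pairs works in the conservative direction. This stands too.

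Third, it is tempting to argue that the centres' own physicians determine the outcome through their certificates. The Setting section says that certificates are a basis for benefit decisions, and that the insurance agency itself assesses entitlement after 90 days and may do so again at day 180. Correlation within centres is plausible, but its size cannot be read from the text.

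Finally, the Discussion already concedes that a difference will be hard to detect. That concession concerns the number of patients and not the clustering.

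**Conclusion.** The point holds in conditional form. It is certain, by reproduction, that the power range makes no allowance for randomising centres and is therefore optimistic for any positive ICC, unless effective matching is used in the analysis to recover the loss. At ICC 0.05, ignoring matching, the lowest power is about 34% (equal clusters) or 30% (CV 0.8), and power at a 20% control rate is about 64% or 58%.

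It is not established that the final analysis will ignore centre. If it does, the type I error may exceed 5%: about 5.6% to 11% with equal clusters and ICC 0.01 to 0.10, or 6% to 15% with CV 0.8. In the simulation it was about 6% to 9% at ICC 0.05 and 7% to 12% at ICC 0.10, the lower ends applying when the pairs explain most of the between-centre variance. ICC, CV and the strength of the matching are all assumptions.

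**What to change.** State, before the outcome data are analysed, a primary analysis that is valid for the randomised units. Options:

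- a within-pair permutation test over the 2^11 = 2048 possible allocations; or
- a mixed model or GEE with clustering by centre and a small-sample correction.

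Fix the degrees of freedom to match the model: about 22 − 11 − 1 = 10 if pair is a fixed term, about 22 − 2 = 20 if pairs are not modelled. The two should not be mixed: using the t(20) critical value of 2.086 where t(10) applies (2.228) gives about 6.4% type I error.

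Say how a pair with an empty centre is handled, because it carries no within-pair contrast under a fixed pair term. Report the estimated ICC. Restate the power in the sample size section with a design effect over a stated ICC range.

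The cost is wording and code, with no new data. The confidence interval becomes somewhat wider and the stated power lower.

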## Abstract

**Background:**

Work-related stress has become a major challenge for social security and health care systems, employers and employees across Europe. In Sweden, sickness absence particularly due to stress-related disorders has increased excessively in recent years, and the issue of how to improve sustainable return to work in affected employees is high up on the political agenda. The literature on interventions for return to work in patients with common mental disorders is still inconclusive. This randomized controlled trial (RCT) aims to contribute with knowledge about how physicians and rehabilitation coordinators in primary health care can involve the employer in the rehabilitation of patients with stress-related disorders. The objective is to evaluate whether the early involvement of the patient’s employer can reduce the time for return to work compared to treatment as usual. A process study will complete the RCT with information about what prerequisites primary health caregivers need to succeed with this endeavor.

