## Methods/Design

### Aim

The overall aim of this study is to evaluate whether a systematic procedure of cooperation between GPs and RCs which involves the employer can reduce the time for RTW in patients with stress-related disorders during a 12-month follow-up period. An intervention group will be compared to treatment as usual (TAU). The primary hypothesis is that an early contact between caregiver, patient and employer can stimulate the employer to take measures at the workplace that advance patients’ RTW. However, we expect this relationship to depend on various circumstances, both at the patient and the organizational level, such as the patient’s symptom severity and motivation to RTW, and the participant GPs’ and RCs’ possibilities to adhere to the intervention.

The second aim of the study is to investigate the organizational prerequisites for primary health care centers (PHCC) to involve the employer at an early stage of rehabilitation. This will be done by a process evaluation, using interviews and register data at the center level.

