### Setting

In Sweden, county councils are responsible for providing primary health care. Caregivers that comply with regional standards have the right to provide primary health care, and for a modest fee of € 10, citizens have the right to seek care among both public and private suppliers, funded by public means. One important task for Swedish GPs is to issue the sickness certificates that serve as a basis for social insurance benefit assessments, required from the 8^th^ day of a sick-leave period. A sick-leave certificate must contain a large amount of detailed information, for example about the patient’s diagnosis; functional impairments and activity limitation (work incapacity). The physician can seek advice on appropriate sick-leave durations for different diagnoses in a national decision support, issued by the National Board of Health and Welfare to enhance equal treatment over regions and caregivers. The work capacity must be reduced by at least 25 % for the employee to qualify to sickness benefits. The first fourteen days of a sick-leave period is covered by the employer (except for a first qualifying day), thereafter the Social Insurance Agency takes over the financial responsibility [29]. After 90 days of sick-leave, the agency decides on the right to further payments by assessing the employee’s work capacity in relation to all other work tasks offered by the employer. Further benefits are only granted if there are no such possibilities. The employee has the right to be off duty to try another job, with another employer. At day 180, the employee’s work capacity is evaluated in relation to the entire labour market, but only if it can be assumed that the patient will not be able to return to his or her ordinary job before day 365, or if there are other reasonable conditions that inhibit evaluation. Sickness benefits can compensate for an income loss corresponding to 25 %, 50 %, 75 % or 100 % of the employee´s working hours.

The study is conducted in the Västra Götaland region of Sweden, a large county council covering almost 20 % of the Swedish population with 200 public and private PHCCs. There are about 800 GPs employed at these PHCCs and almost all centers can offer the services of a RC. However, coordinators depend on earmarked national subsidies, and it is common for the coordinator to either work part time as for example a nurse or psychologist, or to work as a coordinator at two or even three centers.

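### The aim is a shorter time to return to work, but the only stated group comparison is the proportion on any sick leave at three time points, a coarse proxy for time

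*Protocol article*

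**What the plan says.** The abstract's background gives the objective as whether early employer involvement "can reduce the time for return to work compared to treatment as usual". The Aim section asks whether the procedure "can reduce the time for RTW in patients with stress-related disorders during a 12-month follow-up period". The abstract's discussion and the main Discussion also describe the goal as less time to RTW.

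Under Outcome measurements and statistical analyses the article states "The primary outcome of the RCT is RTW", without attaching a time metric. It then gives one comparison between the arms: the difference "in proportion of patients on full- or part-time sick leave at three, six and 12 months after inclusion". The abstract's methods paragraph names the same comparison, and the Sample size section computes power for it. The data come from the MiDAS register, "where all sick-leaves exceeding two weeks are registered". The Setting section adds: "Sickness benefits can compensate for an income loss corresponding to 25 %, 50 %, 75 % or 100" per cent of working hours.

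**The concern.** The question is about duration and the stated analysis is about status at three times since inclusion. Three things are lost.

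- **Timing within intervals.** A return on day 20 and one on day 89 look the same at month 3. The Background section gives an average of 57 days to end a sick-leave case in this diagnosis group. That clock starts at the beginning of the case, whereas inclusion is at certificate renewal, so the figure does not transfer directly. It does suggest that a good share of returns may precede the first snapshot.
- **Degree.** Leave at 25 % and at 100 % count alike. The intervention ends with a meeting to plan RTW. If that plan is a stepwise return, the steps earn no credit.
- **Sustainability.** A patient who is off leave on the date may have returned for good or may be between spells.

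At stake is whether the final report can say anything direct about time to RTW, in a trial whose authors already concede limited power.

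**Working it through.** **1. The plan's own power figure.** Inputs from Sample size: "69 to the control group and 63 to the intervention group", a 15-point difference, two-sided 5 %, and the assumption that "the prevalence of sick-leave in the control group fluctuates between 20 % and 95" per cent. (The section also says 135 recruited; 69 + 63 = 132, the figure used elsewhere in the article.) For control proportion p1, intervention p2 = p1 − 0.15 and pooled proportion p:

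power = Φ{ [0.15 − 1.96·√(p(1−p)(1/69 + 1/63))] / √(p1(1−p1)/69 + p2(1−p2)/63) }

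This gives 74.0 % at p1 = 20 %, 41.2 % at 50 %, a minimum of 40.5 % near 57.5 %, and 75.0 % at 95 %. The stated 41 % to 74 % is reproduced to within about a point. It is the power of one snapshot comparison, not of a test of time to RTW.

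**2. What equal snapshots can hide (illustrative assumptions).**
- Timing: if a fraction f of each arm returns before month 3 and the intervention arm does so 30 days sooner, mean time differs by 30f days. For f = 30-50 % that is 9-15 days per patient, with no difference at any snapshot.
- Degree: a patient on 100 % leave for 365 days has 365 net days. One who drops to 25 % at day 60 and stays there has 60 + 0.25 × 305 = 136 net days. Both are on leave at all three snapshots.

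**3. Power of a time-to-RTW analysis.** Assumptions not in the documents: exponential times, proportional hazards, no relapse, no clustering, complete follow-up to month 12. Let S be the control proportion still on leave at month 6, with a 15-point difference there. The hazard ratio for RTW is HR = ln(S − 0.15)/ln S. Expected events are D = 69(1 − S²) + 63(1 − (S − 0.15)²). Schoenfeld power is Φ{ √(D·(63/132)·(69/132))·ln HR − 1.96 }. Snapshot power uses the formula in step 1 with the proportions that this model implies at months 3, 6 and 12.

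| S at month 6 | HR | Events | Log-rank | Month 3 | Month 6 | Month 12 | Gain over month 6 | Gain over best snapshot |
|---|---|---|---|---|---|---|---|---|
| 30 % | 1.58 | 124 | 71.7 % | 45.3 % | 53.7 % | 37.8 % | 18.0 | 18.0 |
| 40 % | 1.51 | 117 | 60.9 % | 33.4 % | 44.9 % | 42.0 % | 16.0 | 16.0 |
| 50 % | 1.51 | 107 | 57.3 % | 28.4 % | 41.2 % | 46.3 % | 16.1 | 11.0 |
| 60 % | 1.56 | 94 | 58.2 % | 26.5 % | 40.6 % | 51.7 % | 17.6 | 6.5 |
| 70 % | 1.68 | 79 | 63.1 % | 26.8 % | 42.9 % | 59.5 % | 20.2 | 3.6 |

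**4. Sensitivity to proportional hazards.** Simulation with 20,000 trials per setting, the same exponential control times and 15 points at month 6:
- Hazards equal after month 6: for S = 40/50/60/70 %, log-rank power is about 41/34/31/32 %, against 45/42/41/44 % for the six-month snapshot. The snapshot is better.
- No effect before month 3, persisting afterwards: at S = 50 % log-rank has about 66 % and the 12-month snapshot 72 %. At S = 60 % the figures are 73 % and 80 %.

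**The case against.** The strongest defence is that proportions still on leave at three, six and 12 months are three points on the sick-leave curve, so a faster return should lower them. The outcome section, the abstract's methods and the power statement agree with one another, and only the wording of the aim is loose. Counting any remaining leave as not returned is a legitimate and explicit definition. Duration analyses may also stand in a full plan that is not shown.

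Much of this stands. A reader might infer that the trial cannot answer its question at all. The documents do not support that, because the snapshots are a weak proxy for time, not an irrelevant one. A reader might also infer that the snapshots necessarily waste power, and step 4 shows that this depends on the shape of the effect. Nor does it follow that the primary outcome must be replaced. Recruitment closed in January 2018 and centre staff know their allocation, so changing the primary now carries its own risk. Making full RTW primary would also not cure the part-time problem, because a patient on 25 % leave would still count as not returned.

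What does not fall away is the mismatch itself. The article fixes its group comparison in three places as something other than the duration named in its aim. A later plan that followed the article would inherit this.

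**Conclusion.** The point holds as an inconsistency between aim and analysis: no between-group analysis stated in the article estimates time to RTW or credits a reduced degree of leave. This conclusion needs no distributional assumption.

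The efficiency argument is secondary and conditional. Under the step 3 assumptions the log-rank test gains 16-20 points over the six-month snapshot, but only 3.6-6.5 points over the best snapshot at 60-70 % on leave, and it loses if the effect is early only or late. Clustering by centre would lower power for both approaches.

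Two inferences should be declared. That MiDAS supplies spell dates is not stated, but status at fixed times could not be read without them. That it supplies degree is inferred from the planned full- or part-time reading and the graded benefit. Spells of two weeks or less are not registered, so neither approach sees them.

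**What to change.** Before outcomes are linked to allocation:

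1. Keep the three prevalences as the primary comparison and word its conclusion as prevalence of sick leave, not time to RTW.
2. Pre-specify two key secondary analyses from the same MiDAS extract:
   - (a) Time from inclusion to sustained full RTW. Fix in advance the length of the run without registered sick leave (for example 28 days), censor at 12 months, allow for centre clustering (for example a Cox or discrete-time hazard model with centre frailty) and check proportional hazards.
   - (b) Net sick-leave days over 12 months, weighted by degree if the extract holds it. This is the analysis that credits part-time return.
3. Rest any statement about time to RTW on (a) and (b).
4. State that spells of two weeks or less are invisible, so a run without registered leave may contain them, and confirm that spell dates and degree are in the extract.

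Cost: a few lines of plan text, a little more analysis, and disclosure of the added outcomes against the registration. No new patients, visits or data source should be needed if the extract holds the dates and degree.
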